## Appendix 2: Notable laboratory value criteria, special methods and scales

| Laboratory variable                                        | Standard units                                                                                                                                         | SI units                                                                                                                                                       |
|------------------------------------------------------------|--------------------------------------------------------------------------------------------------------------------------------------------------------|----------------------------------------------------------------------------------------------------------------------------------------------------------------|
| Liver function and related variables                |                                                                                                                                                        |                                                                                                                                                                |
| SGOT (AST)                                                 | $\geq 3 \times \text{ULN}$                                                                                                                             | $\geq 3 \times \text{ULN}$                                                                                                                                     |
| SGPT (ALT)                                                 | $\geq 3 \times \text{ULN}$                                                                                                                             | $\geq 3 \times \text{ULN}$                                                                                                                                     |
| Bilirubin                                                  | $\geq 3 \times \text{ULN}$                                                                                                                             | $\geq 3 \times \text{ULN}$                                                                                                                                     |
| Renal function, metabolic and electrolyte variables |                                                                                                                                                        |                                                                                                                                                                |
| Urea                                                       | None                                                                                                                                                   | None                                                                                                                                                           |
| Creatinine                                                 | Day 8 or after:
>30% above value from preceding visit
or
Day 8 to Wk 4: $\geq 4 \text{ mg/dL}$ ,
After Wk 4: $\geq 3 \text{ mg/dL}$ | Day 8 or after:
>30% above value from preceding visit
or
Day 8 to Wk 4: $\geq 354 \mu\text{mol/L}$ ,
After Wk 4: $\geq 265 \mu\text{mol/L}$ |
| Uric acid                                                  | M $\geq 12 \text{ mg/dL}$
F $\geq 9 \text{ mg/dL}$                                                                                                  | M $\geq 714 \mu\text{mol/L}$
F $\geq 535 \mu\text{mol/L}$                                                                                                   |
| Glucose                                                    | <45 mg/dL
>250 mg/dL                                                                                                                                | <2.5 mmol/L
>13.9 mmol/L                                                                                                                                    |
| Cholesterol                                                | $\geq 350 \text{ mg/dL}$                                                                                                                               | $\geq 9.1 \text{ mmol/L}$                                                                                                                                      |
| Triglycerides                                              | $\geq 750 \text{ mg/dL}$                                                                                                                               | $\geq 8.5 \text{ mmol/L}$                                                                                                                                      |
| CPK (MB)                                                   | None                                                                                                                                                   | None                                                                                                                                                           |
| Potassium                                                  | $\leq 3.0 \text{ mEq/L}$
$\geq 6.0 \text{ mEq/L}$                                                                                                   | $\leq 3 \text{ mmol/L}$
$\geq 6 \text{ mmol/L}$                                                                                                             |
| Calcium                                                    | $\leq 6 \text{ mg/dL}$
$\geq 13 \text{ mg/dL}$                                                                                                      | $\leq 1.5 \text{ mmol/L}$
$\geq 3.2 \text{ mmol/L}$                                                                                                         |
| Hematology variables                                |                                                                                                                                                        |                                                                                                                                                                |
| Hemoglobin                                                 | <7 g/dL                                                                                                                                                | <4.39 mmol/L                                                                                                                                                   |
| Platelets
(thrombocytes)                                | <50 $\text{k/mm}^3$
$\geq 700 \text{ k/mm}^3$                                                                                                       | <50 $\times 10^9/\text{L}$
$\geq 700 \times 10^9/\text{L}$                                                                                                  |
| Leukocytes
(WBCs)                                       | $\leq 2.0 \text{ k/mm}^3$
$\geq 16 \text{ k/mm}^3$                                                                                                  | $\leq 2.0 \times 10^9/\text{L}$
$\geq 16 \times 10^9/\text{L}$                                                                                              |
| Hematology variables: differential                  |                                                                                                                                                        |                                                                                                                                                                |
| Granulocytes (poly,
neutrophils)                        | $\leq 1,000/\text{mm}^3$                                                                                                                               | $\leq 1 \times 10^9/\text{L}$                                                                                                                                  |
| Eosinophils                                                | $\geq 12\%$                                                                                                                                            | $\geq 12\%$                                                                                                                                                    |
| Lymphocytes                                                | $\leq 1,000/\text{mm}^3$                                                                                                                               | $\leq 1 \times 10^9/\text{L}$                                                                                                                                  |

---

| Harmonized notable vital signs (and weight) |                                                                                                                                                                 |
|---------------------------------------------|-----------------------------------------------------------------------------------------------------------------------------------------------------------------|
| Vital sign variables                        | Notable criteria                                                                                                                                                |
| Pulse (beats/min.)                          | None                                                                                                                                                            |
| Systolic BP (mm/Hg)                         | Either an increase of $\geq 30$ that results in $\geq 180$ or $>200$ (mm/Hg)
or
Either a decrease of $\geq 30$ that results in $\leq 90$ or $<75$ (mm/Hg) |
| Diastolic BP (mm/Hg)                        | Either an increase of $\geq 20$ that results in $\geq 105$ or $>115$ (mm/Hg)
or
Either a decrease of $\geq 20$ that results in $\leq 50$ or $<40$ (mm/Hg) |
| Weight (Kg)                                 | None                                                                                                                                                            |

---

## Appendix 3: Possible drug interactions

All of the individual drugs cited below are well substantiated to interact with cyclosporine. In addition, concomitant non-steroidal anti-inflammatory drugs, particularly in the setting of dehydration, may potentiate renal dysfunction.

### Drugs that may potentiate renal dysfunction

| Antibiotics                                                                  | Antifungals                                       | Gastrointestinal agents  |
|------------------------------------------------------------------------------|---------------------------------------------------|--------------------------|
| Gentamicin
Tobramycin
Vancomycin
Trimethoprim with-sulfamethoxazole | Amphotericin B
Ketoconazole                    | Cimetidine
Ranitidine |
| Antineoplastics                                                              | Anti-inflammatory drugs                           | Immunosuppressives       |
| Melphalan                                                                    | Azapropazon
Diclofenac
Naproxen
Sulindac | Tacrolimus               |

### Drugs that alter cyclosporine concentrations

Cyclosporine is extensively metabolized. Cyclosporine concentrations may be influenced by drugs that affect microsomal enzymes, particularly cytochrome P-450 III-A. Substances that inhibit this enzyme could decrease metabolism and increase cyclosporine concentrations. Substances that are inducers of cytochrome P-450 activity could increase metabolism and decrease cyclosporine concentrations. Monitoring of circulating cyclosporine concentrations and appropriate Sandimmun® Optoral dosage adjustments are essential when these drugs are used concomitantly.

### Drugs that increase cyclosporine concentrations

| Calcium channel blockers              | Antifungals                                               | Antibiotics                    |
|---------------------------------------|-----------------------------------------------------------|--------------------------------|
| Diltiazem
Nicardipine
Verapamil | Ketoconazole
Fluconazole
Itraconazole               | Clarithromycin
Erythromycin |
| Glucocorticoids                       | Other drugs                                               |                                |
|                                       | Allopurinol
Bromocriptine
Danazol
Metoclopramide |                                |

Grapefruit and grapefruit juice affect cyclosporine metabolism, increasing blood concentrations of cyclosporine, thus should be avoided.

### **Drugs that decrease cyclosporine concentrations**

| Antibiotics    | Anticonvulsants                      | Other drugs                        |
|-----------------------|---------------------------------------------|-------------------------------------------|
| Nafcillin
Rifampin | Carbamazepine
Phenobarbital
Phenytoin | Octreotide
Ticlopidine
Troglitazone |

Rifabutin is known to increase the metabolism of other drugs metabolized by the cytochrome P-450 system. The interaction between rifabutin and cyclosporine has not been studied. Care should be exercised when these two drugs are administered concomitantly.

### **Other drug interactions**

Reduced clearance of prednisolone, digoxin and lovastatin and simvastatin has been observed when these drugs are administered with cyclosporine. In addition, a decrease in the apparent volume of distribution of digoxin has been reported after cyclosporine administration. Severe digitalis toxicity has been seen within days of starting cyclosporine in several patients taking digoxin. Cyclosporine should not be used with potassium-sparing diuretics because hyperkalemia can occur.

During treatment with cyclosporine, vaccination may be less effective. The use of live vaccines should be avoided. Myositis has occurred with concomitant lovastatin and simvastatin, frequent gingival hyperplasia with nifedipine, and convulsions with high dose methylprednisolone.

### **Population screen for co-medications influencing everolimus (Certican®)**

Patients concomitantly receiving erythromycin antibiotics (erythromycin or azithromycin) had an average 20% lower everolimus CL/F than those not receiving these co-medications. A single patient receiving itraconazole had a 3-fold lower everolimus CL/F compared with the population average. These observations indicate that potent inhibitors of CYP3A can decrease the clearance of everolimus and increase its blood levels.

Additional drugs or drug classes explored in the population model for which no influence on everolimus CL/F was detected were: atorvastatin (n=74 patients), pravastatin (n=41), simvastatin (n=18), gemfibrozil (n=10), quinolone antibiotics (n=124), Bactrim® (n=450), and various calcium-channel blockers (dihydropyridines, n=267, diltiazem, n=22 and verapamil, n=5).

## Appendix 4: Dose Reduction of Certican® and Myfortic®

Dose reduction or temporary interruption may be performed for Myfortic® or Certican®. However, Certican® should be continued on a stable dose level, if possible, and reduced or interrupted only if the symptoms do not respond to the reduction of the Myfortic® dosage.

Implementation of dose reduction will be based on thrombocytopenia, leukopenia, neutropenia, hyperscholesterolemia, hypertriglyceridemia, or other adverse events which are suspected to be related to study medication, and in the opinion of the investigator, are clinically warranted. The following guidelines should be used for both dose reduction and restarting or increasing the dose of study medication back to original levels.

### Dose Reduction Guidelines

#### Platelets

- platelet count < 100,000/mm^3    dose **may** be reduced at the discretion of the investigator
- platelet count < 75,000/mm^3    a second dose reduction should be **considered**
- platelet count < 50,000/mm^3    **MANDATORY** interruption of medication

#### WBC

- WBC < 2,500/mm^3    dose may be reduced at the discretion of the investigator  
A second dose reduction may be implemented if the WBC continues to fall

| Dose Reduction         | Myfortic®                                  |
|------------------------|--------------------------------------------|
| Maintenance dose       | 2 tablets 360 mg b.i.d.                    |
| Initial dose reduction | 1 tablets 360 mg + 1 tablets 180 mg b.i.d. |
| Second dose reduction  | 2 tablets 180 mg b.i.d.                    |

## **Increase or restart of study medication after a drop in platelets / WBC**

### **Increase dose of study medication following a single dose reduction**

After a single dose reduction, full dose of study medications **must** restart if:

- platelet count  $> 100,000/\text{mm}^3$  (at least 3 days)
- WBC  $> 3,500/\text{mm}^3$  (at least 3 days)

### **Increase dose of study medication following a double dose reduction**

After a double dose reduction the mid dose of study medications **may** be restarted if:

- platelet count  $> 75,000/\text{mm}^3$  (at least 3 days)
- WBC  $> 3,500/\text{mm}^3$  (stable) (at least 3 days)

the full dose of study medications **must** be restarted if

- platelet count  $> 100,000/\text{mm}^3$  (at least 7 days)
- WBC  $> 3,500/\text{mm}^3$  (stable) (at least 7 days)

### **Restart of dose of study medication following an interruption**

After an interruption of study medications (due to a decrease in platelets/WBC) study medication **may** be restarted at the lowest dose if:

- platelet count  $> 50,000/\text{mm}^3$  (at least 3 days)
- WBC  $> 3,500/\text{mm}^3$  (stable) (at least 3 days)

the mid dose of study medications **may** be restarted if:

- platelet count  $> 75,000/\text{mm}^3$  (at least 3 days)
- WBC  $> 3,500/\text{mm}^3$  (stable) (at least 3 days)

the full dose of study medications **must** be restarted if

- platelet count  $> 100,000/\text{mm}^3$  (at least 7 days)
- WBC  $> 3,500/\text{mm}^3$  (stable) (at least 7 days)

### **Absolute neutrophil count cutoff levels**

A decrease in absolute neutrophil counts (ANC) to less than 1,000/mm^3 should be avoided during the study. The investigator should use his/her discretion to reduce the dose of non-study medication known to be associated with neutropenia or leukopenia (e.g., ganciclovir, trimethoprim-sulfamethoxazole) before considering initiating a reduction in the dose of study medication.

Recommendations for adjusting the dose of study medication in case of a decrease in absolute neutrophil counts are as follows:

ANC < 1,500/mm^3:                      Consider dose reduction (per investigator discretion)

ANC < 1,000/mm^3:                      Mandatory interruption of study medication

Restart of study medication after a drop in ANC that required interruption of study medication

ANC > 1,500/mm^3 for 7 days:        Restart full dose of study medication

### **Lipid cutoff levels**

Evaluations of plasma cholesterol and/or triglyceride levels can result from a number of drugs commonly used in renal transplantation, including study medication, steroids, cyclosporine, and other drugs.

If plasma cholesterol and/or triglyceride levels are found to be elevated, the dosing of all concomitant medication potentially affecting cholesterol and/or triglyceride levels should be re-considered and optimized as appropriate, in addition to providing dietary advice.

If plasma cholesterol and/or triglyceride levels are still found to be elevated and the elevation is confirmed by a second measurement (performed within two weeks under fasting conditions [last meal ≥ 8 hours prior to sampling]) treatment based on the National Cholesterol Education Program Adult Treatment Panel II (NCEP ATP II) guidelines (see Appendix 3) should be instituted. The patient's CHD risk should be assessed as the NCEP ATP II guidelines are based on presence/absence of CHD and number of CHD risk factors.

Treatment of elevated lipids should be maximized prior to dose reduction or interruption of study medication.

Based on the National Cholesterol Education Program (NCEP) guidelines (Appendix 3) the recommendations for treatment of hyperlipidemia prior to reduction/interruption of study medication are as follows:

If Total Cholesterol  $\geq 250$  mg/dL (6.5 mmol/L) and/or

LDL-C  $\geq 160$  mg/dL (4.1 mmol/L):

***Review Concomitant Medication that may potentially contribute to lipid elevations and provide Dietary Instruction (Registered Dietitian)***

[figure not shown]

If Total Cholesterol still  $\geq 250$  mg/dL (6.5 mmol/L) and/or

LDL-C still  $\geq 160$  mg/dL (4.1 mmol/L):

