### **Treatment of hyperlipidemia**

Lipid lowering medications (e.g., fluvastatin, Lescol®) are to be administered for patients with increased LDL-cholesterol and triglyceride levels following the National Cholesterol Educating Program (NCEP) guidelines ([Appendix 5](#)). Lipid lowering medications should be maximized prior to reduction of Certican®. If the elevation of cholesterol and/or triglyceride levels persists, the dosing of Certican® will be adjusted following the recommendations in [Appendix 4](#).

When HMG-CoA reductase inhibitors are used concomitantly with gemfibrozil (and probably other fibrates), cyclosporine or erythromycin, myopathy and rhabdomyolysis have been reported. Caution is advised if the use of such combinations is deemed necessary.

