***Institute Statin (HMG CoA Reductase Inhibitor, e.g. Lescol®) Therapy Unless Contraindicated***

[figure not shown]

If Total Cholesterol still  $\geq 250$  mg/dL (6.5 mmol/L) and/or

LDL-C still  $\geq 160$  mg/dL (4.1 mmol/L):

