## Appendix 5: National Cholesterol Education Program Guidelines

| Total cholesterol                               |                         |                    |
|-------------------------------------------------|-------------------------|--------------------|
| Under 200 mg/dL                                 |                         | Desirable          |
| 200 – 239 mg/dL                                 |                         | Borderline-high    |
| 240 mg/dL and over                              |                         | High               |
| HDL cholesterol                                 |                         |                    |
| Under 35 mg/dL                                  |                         | Low                |
| Treatment based on LDL cholesterol              |                         |                    |
| Diet Therapy                             | Initiation Level | LDL Goal    |
| Without CHD and with fewer than 2 risk factors* | 160 mg/dL or over       | Under 160 mg/dL    |
| Without CHD and with 2 or more risk factors*    | 130 mg/dL or over       | Under 130 mg/dL    |
| With CHD                                        | Over 100 mg/dl          | 100 mg/dL or under |
| Drug Treatment                           | Initiation Level | LDL Goal    |
| Without CHD and with fewer than 2 risk factors* | 190 mg/dL or over       | Under 160 mg/dL    |
| Without CHD and with 2 or more risk factors*    | 160 mg/dL or over       | Under 130 mg/dL    |
| With CHD                                        | Over 130 mg/dl          | 100 mg/dL or under |

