### \*CHD Risk Factors:

#### Positive

- Age: Men  $\geq 45$  yrs  
Women  $\geq 55$  yrs or premature menopause without estrogen replacement therapy
- Family history of premature CHD (definite myocardial infarction or sudden death before 55 yrs of age in father or other male first-degree relative, of before 65 yrs of age in mother or other female first-degree relative)
- Current cigarette smoking
- Hypertension (Blood pressure  $\geq 140/90$  mmHg [confirmed by measurements on several occasions] or taking antihypertensive medication)
- HDL Cholesterol  $< 35$  mg/dL (0.6 mmol/L)  
(confirmed by measurements on several occasions)
- Diabetes mellitus

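### Appendices 4 and 5 give different lipid-treatment thresholds, so for some patients the protocol both calls for and does not call for drug treatment (minor; primary analysis unaffected)

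*Protocol*

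**What the plan says.** Three places in the protocol govern lipid treatment.

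- **Section 6.5.3, Treatment of hyperlipidemia.** Lipid-lowering drugs are to be given "following the National Cholesterol Educating Program (NCEP) guidelines", with a reference to Appendix 5. They are to be maximized before Certican is reduced, and Certican adjustment is referred to Appendix 4.
- **Appendix 5.** This is the guideline table. Drug treatment starts at LDL "190 mg/dL or over" (no CHD, fewer than 2 risk factors), "160 mg/dL or over" (no CHD, 2 or more) or above 130 mg/dL (CHD). The LDL goals are below 160, below 130, and 100 or under.
- **Appendix 4, Lipid cutoff levels.** The text first directs confirmed elevations to the same guideline and asks for the patient's CHD risk to be assessed, because the "NCEP ATP II guidelines are based on presence/absence of CHD and number of CHD risk factors". It then gives a stepwise ladder, described as guideline-based and introduced as "recommendations for treatment of hyperlipidemia prior to reduction/interruption of study medication are as follows". After the dietary step, if total cholesterol is still >= 250 mg/dL and/or LDL still >= 160 mg/dL, the step is "Institute Statin (HMG CoA Reductase Inhibitor, e.g. Lescol®) Therapy Unless Contraindicated". Later steps use the same two values, with triglycerides >= 600 mg/dL added towards the end. The last step is to consider reducing or interrupting study medication.

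Appendix 4 twice gives Appendix 3 as the location of the guideline. Appendix 3 is the list of drug interactions. Among its risk factors, Appendix 5 lists HDL below 35 "mg/dL (0.6 mmol/L"). Appendix 7 puts the same 35 mg/dL cut-off at 0.90 mmol/L.

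**The concern.** The ladder and the table claim one source but do not give the same instruction. The table splits patients by CHD and number of risk factors; the ladder does not. Two sites could each follow the protocol and treat the same patient differently.

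Two things depend on this. Study-medication reduction for raised lipids may be considered only once lipid treatment has been maximized, and the two appendices imply different points at which that is so. LDL is also an input to the Framingham score (Section 7.6), whose change is a safety variable (Section 10.5.2). The HDL unit error adds to this, because low HDL helps to decide a patient's risk class in Appendix 5.

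**Working it through.** The protocol states no figure to reproduce here, so the check sets the rules side by side.

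**1. Drug start and goals, by LDL (mg/dL), with total cholesterol below 250**

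| Appendix 5 class | Appendix 5 drug start | Appendix 4 statin start | LDL where they differ | Appendix 5 goal | LDL where Appendix 4 no longer escalates but the goal is unmet |
|---|---|---|---|---|---|
| No CHD, < 2 risk factors | >= 190 | >= 160 | 160-189 (Appendix 4 only) | < 160 | none |
| No CHD, >= 2 risk factors | >= 160 | >= 160 | none | < 130 | 130-159 |
| CHD | > 130 | >= 160 | 131-159 (Appendix 5 only) | <= 100 | 101-159 |

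The last column also assumes triglycerides below 600 mg/dL. Diet start differs too: in Appendix 5 it is at LDL 130 or over (2 or more risk factors) and above 100 (CHD), against 160 in the ladder.

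**2. Total cholesterol.** The ladder also acts on total cholesterol >= 250 mg/dL, which is not a trigger in Appendix 5. A CHD patient at LDL 131-159 with total cholesterol >= 250 is treated under both, so that conflict disappears. A patient without CHD, LDL below 160 and total cholesterol >= 250 gets a statin under the ladder only, so a conflict appears.

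**3. Study-medication step.** The end of the ladder, and the paragraph that follows it, name LDL >= 160 mg/dL among the values for considering dose reduction. The table of bands that comes next uses only total cholesterol (250-750 and above 750 mg/dL) and triglycerides (600-1000 and above 1000 mg/dL). A patient with LDL >= 160, total cholesterol below 250 and triglycerides below 600 meets the ladder's condition but falls in no band.

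**4. HDL units.** Appendix 4 equates 250 mg/dL of cholesterol with 6.5 mmol/L, so 1 mmol/L = 250 / 6.5 = 38.5 mg/dL. Then 0.6 x 38.5 = 23.1 mg/dL, and 35 / 38.5 = 0.91 mmol/L, which agrees with Appendix 7 (0.90) and not with Appendix 5 (0.6). A site working in mmol/L from Appendix 5 would not count HDL of about 24-34 mg/dL as a risk factor. All patients are over 65 and so already have the age factor. For a patient without CHD whose only second factor is low HDL, missing it moves the Appendix 5 drug start from 160 to 190.

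**5. Framingham points (Appendix 7).** A fall in LDL from 160-189 to 100-159 changes the score by 1 point in men and 2 in women. A fall from 100-159 to below 100 changes it by 3 in men and 2 in women.

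**The case against.** The best defence is that the two appendices have different jobs. Section 6.5.3 gives lipid treatment to Appendix 5 and Certican adjustment to Appendix 4. The ladder is introduced as what comes before a change of study medication, and Appendix 4 itself asks for a risk-based assessment first. Nor does the ladder say that a statin may start only at its values. On that reading, a CHD patient at LDL 131-159 is already covered by the guideline.

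This has weight and softens the CHD case. It does not remove the conflict. The ladder orders diet and statin steps for the same patients, names the same guideline, and ignores the risk assessment that has just been requested. For a patient without CHD, with fewer than 2 risk factors and LDL 160-189, the ladder starts a statin and the table does not.

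Other limits also stand. Appendix 5 contains no study-medication trigger, so there are not two competing ones; the link to dose reduction runs through the requirement to maximize lipid treatment first. The study-medication steps leave much to the investigator. The HDL value is a slip in parentheses beside a clear mg/dL figure, and it matters only to a site using mmol/L and a patient at the boundary between one and two risk factors.

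**Conclusion.** The instructions are inconsistent as written and should be reconciled, at minor severity. Identifiable patients get opposite drug-start instructions, and goals and escalation differ for two of the three risk classes. In the class without CHD and with 2 or more risk factors, drug start agrees. That class may be large, since age already supplies one factor, but the documents give no shares, so the number of patients affected cannot be stated.

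A reader might infer two stronger conclusions that the documents do not support.

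- **A twofold effect on the Framingham endpoint.** Appendix 7 does give a man aged 70-74 with no other points 7 points (14%), and 7 - 3 = 4 points (7%) if LDL falls below 100. But the protocol describes the score as the risk of developing coronary disease, while the treatment goal in that example is the one for patients who already have it. The example also assumes LDL below 100, whereas the goal is 100 or under and LDL of exactly 100 still scores 0. One constructed patient is not a group change.
- **An imbalance between arms.** The Background reports hypercholesterolemia in more than 10% of patients on everolimus, but it also says that cyclosporine favors hyperlipidemia, and Appendix 4 lists cyclosporine among the causes.

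The primary GFR analysis and the sample size are unaffected.

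**What to change.** - Reconcile Section 6.5.3, the lipid section of Appendix 4 and Appendix 5 so that one consistent set of initiation levels and goals applies to both arms. Which values to use is for the sponsor and clinical investigators; this review proposes none.
- State separately which persisting lipid values prompt consideration of a study-medication change, make the ladder and the table of bands in Appendix 4 agree on whether LDL is one of them, and say when lipid treatment counts as maximized.
- Change both Appendix 3 references in that section to Appendix 5.
- Make the mg/dL and mmol/L values for low HDL in Appendix 5 agree with each other and with Appendix 7.

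The cost is protocol wording: no added tests, and no change to the sample size or the primary analysis.
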